### Measurement of biomarkers

In Module 2 of the project (Fig. 2), a two-phase approach for the biomarker measurement is used: in phase 1, established and novel biomarkers are determined in a set of population cohorts from different European regions, including 90,000 subjects with 6,000 incident acute coronary events, 3,800 incident strokes, 3,500 incident cases of heart failure, 2,600 cases with incident atrial fibrillation and 2,800 incident type 2 diabetes diagnoses during follow-up (Table 1). In addition, markers which are considered as most innovative but “high risk” markers, such as metabolites, miRNA and other novel markers derived from omics approaches will be measured in a case-cohort set of up to 20,000 population-based subjects including 4,500 incident acute coronary events. This case-cohort design reduces the number of biomarker measurements without substantially reducing statistical power [19]. The case-cohort study involves a random subsample of the selected population cohorts and in addition all incident cases of these cohorts (Table 6). Independent of the population-based cohorts, the selected biomarkers are also measured in the four diseased cohorts (n = 8,746, Table 3).

**Table 6 Tab6:** Number of cases and non-cases in the individual case cohort sets of the cohorts selected for the BiomarCaRE case-cohort study

Study	Country	Number of incident cases					Number of non-cases
		Coronary heart disease	Stroke	Heart failure	Atrial fibrillation	Type 2 diabetes	
Glostrup	Denmark	821	744	608	603	526	2,209
ATBC Placebo	Finland	1,414	822	–	–	–	2,068
FINRISK 97	Finland	354	260	442	307	525	1,384
PRIME France	France	286	90	–	–	–	414
KORA S3/S4	Germany	252	224	–	–	390	910
Brianza	Italy	218	119	–	–	–	369
PRIME Belfast	United Kingdom	185	53	–	–	–	282
SHHEC	Scotland	940	411	489	475	477	2,055
Total	4,470	2,723	1,539	1,385	1,918	9,691	

Numbers are given as status in June 2014. ATBC, Alpha-Tocopherol, Beta-Carotene Cancer Prevention Study; FINRISK, FINRISK Study, Glostrup, Glostrup Study; SHHEC, Scottish Heart and Health Extended Cohorts; PRIME, Prospective Epidemiological Study of Myocardial Infarction Study; KORA, Kooperative Gesundheitsforschung in der Region Augsburg; Brianza, The Brianza Study

In phase 2, the most promising biomarkers from phase 1 are further determined in 130,000 subjects from European population cohorts (Table 1). Biomarkers measured within the BiomarCaRE project are depicted in Fig. 3.

### Statistical concepts

BiomarCaRE comprises two closely interacting data centres: one centre that is responsible for the analyses of all population-derived biomarkers which is based at the National Institute for Health and Welfare (THL) in Helsinki; Finland. This data centre has a long-standing and unparalleled experience of epidemiological data harmonization and central data management and analyses of the MORGAM Project [9] and its predecessor, the WHO MONICA Project (Tunstall-Pedoe and Project [32]. The second data centre is based at the University at Lübeck, Germany and is responsible for the analyses of biomarkers derived from the diseased cohorts. Data obtained in clinical trial repositories will be analysed directly at the respective partner site. Figure 4 illustrates and summarizes analyses performed in phases 1 and 2.

**Fig. 4 Fig4:**
[figure not shown]
Overview of data analyses performed in phases 1 and 2 of BiomarCaRE

As biomarkers may have different effects in healthy and diseased subjects, the population-based and diseased cohorts will be analysed separately. The statistical analysis for both types of cohorts will begin with univariate testing of each biomarker with adjustment for classical cardiovascular risk factors. Significant biomarkers are selected for subsequent analysis in phase 2 cohorts for validation.

The risk models are developed using Cox regression analysis, taking the case-cohort sampling into account [19] for some biomarkers. The modelling steps include initial checking of model assumptions and the stability and parsimony of biomarker selection. As a complementary approach for biomarker selection, we will apply random survival forests [13, 15] which is a machine learning technique to determine important variables for the prediction of individual survival times. Performance of the risk estimation models will be cross-validated using calibration, discrimination indices and graphs and net reclassification improvement. The developed predictive models are compared with established risk score models, such as the SCORE [6].

The impact of the biomarkers and the predictive models developed in phase 1 is externally validated using the prospective population-based cohorts and biomarker data from phase 2. These analyses will result in the construction of a risk model including classical risk factors and a combination of the validated biomarkers (BiomarCaRE Panel). As a secondary subsidiary aspect, the cross-sectional association between biomarkers and cardiac imaging data and between biomarkers and health behaviour data will be assessed in individual studies where data are available. Furthermore, joint modelling of repeated measurements of the biomarkers and survival data will be performed for selected cohorts.

To analyze the effects of various pharmacological interventions on the BiomarCaRE panel of selected biomarkers stepwise statistical strategies will be applied in the clinical trials.

In a first step, the predictive value of the BiomarCaRE panel will be assessed in samples from the clinical trials, adjusted for medication and stratified by intervention group. In a second step, the change in biomarker levels from baseline to (on average) 1 year on treatment will be assessed. Finally, the treatment effect will be analyzed according to biomarker levels at baseline (high vs. low).

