## Introduction

Despite significant advances in treatment, cardiovascular disease (CVD) remains the leading cause of death worldwide. Traditional risk factors including dyslipidemia, hypertension, diabetes, obesity, and smoking account for a large proportion of the risk of myocardial infarction and stroke globally [36]. Most of these traditional risk factors are modifiable and their management is likely to reduce risk of CVD in both primary and secondary prevention settings [12]. However, risk estimates based on these classical risk factors only partially explain CVD incidence in the general population and risk estimates vary across European populations. Despite the availability of various global risk assessment scores like the Framingham Score [7], the PROCAM Score [3] and the European Society of Cardiology SCORE [6], prediction of cardiovascular events is incomplete and a considerable number of patients at risk go unidentified on the basis of traditional risk factors alone. Khot et al. [18] have reported that 62 % of patients with MI present with none or only one risk factor and less than 10 % show three or four risk factors. To improve risk estimation above and beyond traditional risk scores, and to improve therapy decision making and guidance, novel (emerging) biomarkers are of considerable interest [4]. A number of those biomarkers are thought to provide additional prognostic information; however, only few studies have evaluated a large panel of biomarkers [4]. Therefore, it is not clear whether these proposed biomarkers might merely be proxies for known risk factors and therefore whether they really provide incremental predictive and discriminatory information. Most importantly, are there so far undetected novel biomarkers that might perform even better than known biomarkers?

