#### Disease cohorts

In patients with manifest CVD, in particular after an acute coronary syndrome (ACS), a number of clinical variables have been proven useful for risk assessment. These variables have been integrated into various scores like the Thrombolysis in Myocardial Infarction (TIMI) Risk Score, and the Global Registry of Acute Coronary Event (GRACE) Score. Based on such parameters fairly reliable prediction can be made not only short-term but even over a period of more than 5 years [11]. However, despite such routinely available variables, further improvement of risk assessment in this high-risk group is of paramount importance because available treatment options should be tailored to the individual patient’s risk. The BiomarCaRE consortium offers the opportunity to directly translate population-derived biomarker information into the clinical setting of manifest CVD and ACS. Within the consortium four disease cohorts comprising almost 9,000 individuals with either angiographically proven stable coronary artery disease (CAD) mostly after myocardial infarction or individuals presenting with suspected acute ACS have been harmonized for CVD history, clinical symptoms and classical cardiovascular risk factor information. The clinical endpoints followed up in the disease cohorts are (1) total mortality, (2) cardiac death, (3) cardiovascular death including fatal cardiovascular events such as cerebrovascular diseases, and (4) cardiovascular events including the combined endpoint of cardiovascular death and non-fatal myocardial infarction (Table 3). The mean age is 61.5 (SD 12.4) years. Follow-up varies between 6 months and 7.5–10 years. Baseline variables are outlined in Table 4. Combining data from different diseases cohorts in BiomarCaRE, in particular from the AtheroGene and KAROLA studies with long-term follow-up, guarantees sufficient power to reliably describe biomarker associations with recurrent cardiovascular events and to test the applicability of a marker panel in diverse clinical settings.

**Table 3 Tab3:** Disease cohorts of BiomarCaRE

Study	Country	Size	Follow-up time (years)	Endpoints				Biomaterial		
				Total mortality	Cardiac death	Cardiovascular death	Cardiovascular events	Serum	EDTA Plasma	DNA
AtheroGene	Germany	3,476	7.5	386	244	260	460	•	•	•
KAROLA	Germany	1,204	10	184	91	103	162	•	•	•
APACE	Switzerland	2,248	2.2	174	71	73	534	•	•	–
stenoCardia	Germany	1,818	0.5	34	0	7	38	•	•	•
Rome ACB*	Italy	500^a^	–	–	–	–		•	•	–

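### In the disease cohorts, biomarkers are screened against classical risk factors only, so a marker that merely tracks disease severity can pass the selection step

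*Protocol article*

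**What the plan says.** Methods, Statistical concepts, says that population-based and diseased cohorts are analysed separately, but gives both the same first step: "The statistical analysis for both types of cohorts will begin with univariate testing of each biomarker with adjustment for classical cardiovascular risk factors". The result is a gate: "Significant biomarkers are selected for subsequent analysis in phase 2 cohorts for validation". Cox models, random survival forests, calibration, discrimination and net reclassification improvement (NRI) follow, and then a benchmark: "The developed predictive models are compared with established risk score models, such as the SCORE". No other score is named there. The final model is described as classical risk factors plus validated biomarkers.

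Methods, Disease cohorts, describes prognosis in manifest CVD differently. It says that "a number of clinical variables have been proven useful for risk assessment", that these are combined in scores such as TIMI and GRACE, and: "Based on such parameters fairly reliable prediction can be made not only short-term but even over a period of more than 5 years". The aim follows from this: "despite such routinely available variables, further improvement of risk assessment in this high-risk group is of paramount importance". The same section says that the four cohorts "have been harmonized for CVD history, clinical symptoms and classical cardiovascular risk factor information".

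**The concern.** The reference set at the selection step does not match the aim that the article states for these patients. Improvement beyond routine clinical variables can be judged only against a model that contains them. The first test contains classical risk factors and, as worded, nothing else, and SCORE is introduced in the article as a global risk score, not as a score for manifest CVD.

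The key established markers include troponins, natriuretic peptides and markers of micronecrosis and renal function. It is plausible that such markers, and novel ones related to them, follow disease severity. If severity is outside the model, some of its effect is credited to the marker. At stake is the meaning of a significant result in the disease cohorts: it would show information beyond classical risk factors, but not beyond what the clinician already has.

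**Working it through.** **The article's own figure.** Table 3 sizes: 3,476 + 1,204 + 2,248 + 1,818 = 8,746. This agrees with Table 4 and with Measurement of biomarkers.

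**Events (Table 3, cardiovascular events).** AtheroGene 460 + KAROLA 162 + APACE 534 + stenoCardia 38 = 1,194. Cardiovascular deaths: 260 + 103 + 73 + 7 = 443.

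**Assumptions, none of them in the article.** Two-sided alpha 0.05; an omitted severity score with hazard ratio (HR) 1.3 to 1.5 per SD; a marker with no effect of its own, whose correlation rho with severity is 0.3 to 0.5 after adjustment for the classical factors.

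**Formulas.**
- Apparent log HR of the marker per SD: b ≈ rho × ln(HR of severity)
- Standard error: SE ≈ 1/√events
- z = b/SE; probability of significance ≈ Φ(z − 1.96) + Φ(−z − 1.96)

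**Apparent effect.**
- Low case: b = 0.3 × ln 1.3 = 0.079, HR 1.08
- High case: b = 0.5 × ln 1.5 = 0.203, HR 1.22

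**Probability that the null marker is significant.**

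| Events used | SE | Low case | High case |
|---|---|---|---|
| All 1,194 pooled | 0.029 | z = 2.7, 78% | z = 7.0, nearly 100% |
| 460 + 162 = 622 | 0.040 | z = 1.96, 50% | z = 5.1, nearly 100% |
| 534 + 38 = 572 | 0.042 | z = 1.88, 47% | z = 4.9, nearly 100% |
| 443 cardiovascular deaths | 0.048 | z = 1.66, 38% | z = 4.3, 99% |

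The second and third rows take AtheroGene and KAROLA as stable coronary disease, and APACE and stenoCardia as suspected acute coronary syndrome. That grouping is also an assumption.

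**Weaker correlation.** With rho = 0.1, severity HR 1.5 and 1,194 events, b = 0.041, z = 1.4 and the probability is 29%.

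**Simulation check.** Cox models with 8,746 patients, 1,194 events, severity HR 2.0 per SD, severity independent of the classical factors, 60 runs per setting:

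| rho | Significant, severity omitted | Significant, severity included |
|---|---|---|
| 0.1 | 53% | 1 of 60 |
| 0.2 | 100% | 1 of 60 |
| 0.3 | 100% | 0 of 60 |

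The severity HR here is stronger than in the first table, so these rates do not extend it. They show the mechanism, and that adjustment for severity removes it.

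**The case against.** The strongest reply is that this is a first screen and not the whole evaluation. The article presents it as the start of the analysis, model building and performance measures follow, and SCORE is given as an example, so a later comparison with TIMI or GRACE is not excluded. This stands, and it limits the wording: a proxy can pass the screen; it is not thereby declared to add value. But no such comparison is named, and it would come after selection.

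A second reply is that a condensed article leaves covariate lists to the analysis plan, that a separate data centre handles the disease cohorts, and that the figure summarising the analyses is not visible. That holds for detail the article omits. It does not hold for the adjustment set, which the article states for both cohort types.

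Third, the Introduction asks only whether markers are proxies for known risk factors ("it is not clear whether these proposed biomarkers might merely be proxies for known risk factors"), in a paragraph on traditional factors. Adjustment for classical factors does address that question. The mismatch is with the aim stated under Disease cohorts.

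A reader might go further and infer either of two stronger points:
- *The plan wrongly merges stable coronary disease with suspected acute coronary syndrome.* Statistical concepts does not say whether the settings are stratified, and an analysis plan may settle it.
- *The panel's cost-effectiveness in secondary prevention would be overstated.* The article builds the panel through external validation in phase 2 population cohorts and takes markers selected from phase 2 into the economic module. A pure severity marker would still have to validate in general populations, and no separate secondary-prevention panel is defined.

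**Conclusion.** The point holds in a limited form. For the disease cohorts, the article fixes a selection test whose covariates leave out the clinical variables that it calls proven, and it names only SCORE as a benchmark. A marker that only reflects severity can therefore be selected in these patients.

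The probabilities are illustrative. They depend on the assumed alpha, severity effect and residual correlation, and on full pooling of events. They fall where the classical factors already capture part of severity. What does not depend on these assumptions is the mismatch between the stated aim and the stated reference set. The change is worth making, but nothing here shows that the final panel or its economic evaluation is wrong.

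**What to change.** For the disease cohorts, change the first-step adjustment set in Statistical concepts to classical cardiovascular risk factors plus the CVD history and clinical symptoms already harmonized, and add TIMI or GRACE components where a cohort holds them. Report added discrimination, calibration and NRI over that clinical model, and not only against SCORE.

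The cost is mainly wording, since at least CVD history and symptoms are available. The article does not show that the TIMI or GRACE components are held, so covariate sets may differ by cohort, and the results should say which set was used. Fewer markers will pass selection in these patients.

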#### Clinical trials

Various biomarkers may be affected by contemporary pharmacological strategies as seen for example in the case of hsCRP and statin treatment [24]. This biomarker may be lowered by 40 % when highly potent statins are given. Thus, it may be important to test the effects of various therapies on our finally selected biomarkers. Based on access to biobanks of several large clinical trials, BiomarCaRE will test biomarkers as measures of therapeutic response related to aspirin in women (Women´s Health Study), LDL-Cholesterol lowering by statins (The Long-Term Intervention with Pravastatin in Ischaemic Disease (LIPID) Study and The Justification for the Use of Statins in Primary Prevention: An Intervention Trial Evaluating Rosuvastatin (JUPITER) trial), and anti-inflammatory treatment with an Lp-PLA2 inhibitor (darapladib) [Integrated Biomarker and Imaging Study-2 (IBIS-2)] (Table 5).

**Table 5 Tab5:** Clinical trials of BiomarCaRE

Study	Setting	Size	Intervention	Median follow up time (years)	Primary endpoint
LIPID	Secondary prevention	9,014	Pravastatin (40 mg)	6.1	CHD Death Non-fatal MI
JUPITER	Primary prevention	17,802	Rosuvastatin (20 mg)	1.9	MI Stroke Cardiovascular death Hospitalization for UAP
WHS	Primary prevention (women only)	39,876	Aspirin (100 mg) every other day	10.1	Non-fatal MI Non-fatal stroke Cardiovascular death
IBIS-2	Secondary prevention	330	Darapladib (160 mg)	1	Coronary atheroma Progression by IVUS Plaque deformability by Palpography hsCRP

Clinical trials of the project are listed including information on trial setting, size, intervention, duration and primary endpoint of trial. LIPID, The Long-Term Intervention with Pravastatin in Ischaemic Disease Study; JUPITER, The Justification for the Use of Statins in Primary Prevention: An Intervention Trial Evaluating Rosuvastatin Trial; WHS, The Women’s Health Study; IBIS-2, Integrated Biomarker and Imaging Study-2; hsCRP, high-sensitivity measured C-reactive protein

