### Economic assessment of single and combined biomarker application

In the third module of the project (Fig. 2), the focus will be on the clinical utilisation and cost-effectiveness of the selected biomarkers, and their single and joint application. Selected biomarkers from phase 2 will be measured in samples of clinical trials to test their interaction with risk lowering therapy (Table 5) and a decision-analytic model will be developed to estimate long-term effectiveness and cost-effectiveness of a primary or secondary preventive strategy based on additional risk assessment using these biomarkers.

Decision-analytic modelling allows for the combination of empirical evidence on improvements in risk prediction and published evidence on short- and long-term effects of health are interventions to estimate the health effects on patient-relevant endpoints such as life expectancy or quality-adjusted life expectancy. Total costs of a strategy will then be estimated by combining cost savings through prevention of advanced disease and costs for the biomarker panel tests, diagnostic tests and work-up, drug treatment and monitoring of patients. A decision-analytic state-transition (Markov) model will be used, as this model type suits decision problems that can be described in specific health states and transition probabilities [5]. The analysis will be performed as a cohort simulation or as a microsimulation depending on the number of covariates to be tracked in the simulation [30], and deterministic and probabilistic sensitivity analyses will be performed. The long-term effectiveness of the biomarker-guided strategies will be expressed in life years and quality-adjusted life years (QALY). Cost-effectiveness will be expressed as incremental cost-effectiveness ratios, that is, the additional costs divided by gains in effectiveness [29]. In particular, we will systematically vary biomarkers and cut-offs in our model to identify candidate strategies for effective and cost-effective biomarker testing that can be investigated in future clinical trials.

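### The trials' treatment-by-biomarker analysis is stated only as a high-versus-low split, although the aim is to test interaction; a continuous interaction test should be the stated method

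*Protocol article*

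**What the plan says.** The end of the Statistical concepts section of the protocol article sets out three steps for the clinical trials.

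- Step one assesses the predictive value of the panel, "adjusted for medication and stratified by intervention group".
- Step two is described as follows: "In a second step, the change in biomarker levels from baseline to (on average) 1 year on treatment will be assessed".
- Step three reads: "Finally, the treatment effect will be analyzed according to biomarker levels at baseline (high vs. low".

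The section on economic assessment states the purpose: "Selected biomarkers from phase 2 will be measured in samples of clinical trials to test their interaction with risk lowering therapy". The Clinical trials section adds a second purpose, to study the markers as measures of therapeutic response.

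Three other places bear on the point. The opening of Statistical concepts says that trial data are analysed at the partner sites, not at the two data centres. Table 5 lists four trials: LIPID (9,014), JUPITER (17,802), WHS (39,876) and IBIS-2 (330). The Discussion calls the clinical trials hypothesis-generating. The article gives no cut-point, interaction term or continuous analysis for step three.

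**The concern.** The aim and the stated method do not fit well. A test of interaction asks whether the treatment effect changes with the level of the marker. Splitting the marker into two groups treats everyone on the same side of the cut as alike, so any gradient within each group is lost. The result also depends on where the cut falls. With analysis at separate sites and no common cut, each trial could define high in its own way, and the results would be hard to set side by side.

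Interaction is usually the question on which a trial has least power. A marker that does modify the treatment effect could be missed at this stage and not taken further. The smallest trial, IBIS-2 with 330 participants, can least afford the loss.

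**Working it through.** **Inputs.** From the document: the high/low form, the absence of a cut-point, and the trial sizes. It states no power, alpha, effect size or efficiency figure for these analyses, so there is no figure of the plan to reproduce. Assumed: a normally distributed marker (for example after log transformation), an interaction linear in the marker, and a two-sided 5% test.

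**Information kept by a split.** For a cut c with a share p of participants below it, and φ the standard normal density, the efficiency of the split relative to a linear term is φ(c)² / [p(1 − p)]. At the median, φ(0)² = 1/(2π) = 0.159 and p(1 − p) = 0.25, so the ratio is 2/π = 0.637. The loss is 36.3%, and equal power would need 1/0.637 = 1.57 times the sample.

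| Group called high | Information kept | Loss |
|---|---|---|
| Top half | 0.637 | 36.3% |
| Top 40% | 0.622 | 37.8% |
| Top third | 0.595 | 40.5% |
| Top quarter | 0.539 | 46.1% |
| Top fifth | 0.490 | 51.0% |
| Top tenth | 0.342 | 65.8% |

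**Power with a median split.** Power = Φ[(1.960 + z) × √0.637 − 1.960], where z is the normal quantile of the power with the continuous marker and √0.637 = 0.798.

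- 80%: 2.802 × 0.798 − 1.960 = 0.276, giving 61%.
- 90%: 3.242 × 0.798 − 1.960 = 0.626, giving 73%.
- 95%: 3.605 × 0.798 − 1.960 = 0.916, giving 82%.

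**Check by simulation.** A linear model with a treatment-by-marker term, 2,000 participants and 3,000 replicates:

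| True interaction | Power, continuous | Power, median split | Information, split/continuous |
|---|---|---|---|
| Linear | 78.8% | 60.9% | 0.64 |
| Step at the median | 60.8% | 80.1% | 1.56 |

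The first row confirms the formula. The second shows that the order reverses when the interaction is a step exactly at the cut. The simulation used a continuous outcome; for event endpoints the ratios should be read as approximate.

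**Step two.** Baseline and one-year values were simulated as bivariate normal with correlation ρ and no drug effect (1,000,000 subjects). The mean change over all subjects is 0.00 SD for every ρ from 0.5 to 0.9. In the half with high baseline values it is −0.40 SD at ρ = 0.5 and −0.08 SD at ρ = 0.9. The difference between arms in that half is at most 0.004 SD in absolute value. Regression to the mean therefore appears only when participants are selected on baseline and the arms are not compared.

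**The case against.** The strongest reply is that this is a condensed article. The cut-point and the exact interaction model are commonly left to a full analysis plan, and reporting effects by high and low does not exclude a formal interaction test on the continuous marker. The stated aim even speaks of testing interaction. Threshold groups also have a use in the decision-analytic model, where cut-offs are to be varied. Much of this stands for the cut-point and for model detail. It does not fully answer the point, because the article did not leave the form open: it named one, and that one is weak for the stated aim under ordinary assumptions.

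It also stands that the loss is conditional. The article gives no cut, distribution or interaction shape, so a reader should not conclude that a third of the information is certainly wasted.

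A reader might further infer from step two that an uncontrolled change from baseline will be taken for drug response, with regression to the mean counted as effect. The document does not support this. Step two neither confines the change to the active arm nor excludes a comparison between arms, and it is not said to be split by baseline level. The steps are introduced as a study of the effects of the interventions. Nor can the variance ratio (1 + ρ)/2, a 15–25% reduction for an assumed ρ of 0.5 to 0.7, be used to size such a fault. It compares a baseline-adjusted analysis with a between-arm difference in change scores, which is already a randomised comparison.

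**Conclusion.** The point holds for step three. The only stated form of the treatment-by-biomarker analysis is a high/low split with no common cut, while the aim is to test interaction. With a normal marker and a linear interaction, even the median, the most favourable cut, keeps about 64% of the information. If the true interaction is a step at the cut, the split is the better choice; the article gives no reason to expect such a step and names no place for one.

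Step two contains no demonstrated error. At most its wording leaves the between-arm contrast unstated.

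Severity is minor to moderate: the trial analyses are hypothesis-generating, and the remedy lies in the wording of the analysis.

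**What to change.** In each trial, make the test of interaction a model with randomised treatment, the continuous baseline biomarker (log scale where suitable) and their product. Check for non-linearity, for example with a spline. Keep the high and low estimates for display only, at a cut fixed beforehand and common across the partner sites.

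As a clarification to step two, state that the one-year change is compared between randomised arms, adjusted for the baseline value.

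The cost is agreed wording across the sites and slightly more analysis work. The change to step three needs no additional samples; the step-two comparison needs none where both arms are assayed. The trade-off is lower power if the true interaction is a step at the cut: about 61% against 80% in the simulated case.
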